### Allocation

2.5

For the nutritional intervention study, patients with AD will be randomly assigned to two groups (*n* = 30 each) using the free randomization software OxMar (26). Randomization will not be stratified by study site. However, the study site will be included as a covariate in the statistical models to control for its potential effect as a confounding variable. The control group will receive a standard nutritional supplement commonly used in patients with AD (Souvenaid^®^, Nutricia, Madrid, Spain), and dietary recommendations will be provided if their usual intake does not meet the established nutritional goals for this population. The intervention group will receive the newly designed supplement, along with tailored dietary recommendations. The group assignment will be performed by the team of neurologists. Supplement blinding in terms of format, flavor, odor, etc., is not planned in this study. Supplements will be labeled as either “A” or “B,” and participants will be informed that they are taking a supplement but will not know whether it is the standard or the “*ad hoc*” formulation. To eliminate bias, the researchers conducting the experiments and performing the analyses will remain blinded to group allocation. Baseline demographic and clinical information will be collected for participants who discontinue the study, along with available data on health status, adverse events, and primary efficacy outcomes.

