This protocol describes a study whose aim is to investigate the feasibility of designing personalized nutritional supplements for patients with AD based on their sex, age, medical history, dietary habits, physical activity, and gut microbiota, applying AI and bioinformatics tools through a data-driven approach. In this context, study success, referred to as “greater efficacy” is defined as promoting a microbiota with a higher presence of health-associated species, reducing microbial taxa related to AD, and modifying AD-related biomarkers. The use of a combination of predictive and causal approaches (including network analysis) to integrate and simultaneously analyze patient clinical data, dietary and exercise habits, and microbiota profiles will allow us to identify dietary variables that should be modified to induce changes in factors related to AD prevention (e.g., butyrate) or progression (e.g., LPS and microbiota markers). The overarching goal is to determine whether such a tailored supplement would exhibit greater efficacy than currently available products. A medical food product designed to support brain health in individuals with AD will be used as a comparator. Finally, the study aims to identify new AD-related markers modified by the designed supplement using a metabolomic approach.

The findings may lead to the development of new, customized nutritional products by food and pharmaceutical companies, offering substantial socio-economic benefits. Moreover, the study’s multidisciplinary approach could advance both Alzheimer’s care and the science of personalized nutrition, providing a model for future research and clinical applications.

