### Interventions

2.2

The study consists of three main stages (Figure 1). At baseline (*T* = 0), both healthy subjects and patients will undergo characterization, including demographic data, physical characteristics (age, sex, BMI, etc.), frailty (Clinical Frailty Scale for Accumulation of Deficits, CFS), malnutrition (Mini Nutritional Assessment questionnaire, MNA), clinical data (biochemistry, hematology, apolipoprotein E (APOE) genotyping, inflammatory markers, etc.), diet, physical activity (International Physical Activity Questionnaire for the Elderly, IPAQ-E), gut microbiota (diversity, composition, and community interactions), blood LPS and butyrate levels, as well as comorbidities and medications. All the collected variables will be subjected to network and predictive analyses (e.g., random forest) to examine interactions between variables and identify modifiable predictors of AD through dietary intervention. In the second stage, a personalized supplement will be designed based on the characteristics of patients with AD, though patients themselves will not be involved in this phase. In the third stage, a randomized, parallel-group nutritional intervention trial will be conducted to compare the “*ad hoc*” designed supplement with a standard nutritional supplement commonly used in patients with AD. The interval between baseline characterization (*T* = 0) and the beginning of the intervention (*T* = 2) will vary depending on recruitment, sequencing, and data processing times. The intervention will start as soon as possible after completion of these analyses, in order to maximize the relevance of the baseline analyses. During this period, participants will continue their usual medical care without changes. The intervention will last 3 months (pre-intervention: *T* = 2; post-intervention: *T* = 3) to evaluate the supplement’s effectiveness in modulating the microbiota, LPS levels, and butyrate production. Additionally, a metabolomic analysis will be conducted to identify new biomarkers related to the supplement’s effects on the disease.

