
### Supplement design

2.20

Patients will be clustered into distinct groups based on the similarity of their baseline gut microbiota composition, clinical markers, and dietary patterns. Dimensionality reduction techniques, e.g., principal component analysis (PCA) or uniform manifold approximation and projection (UMAP) will be applied to reduce noise and identify key features driving interindividual variability. Subsequently, unsupervised clustering algorithms (e.g., k-means, hierarchical clustering, or model-based clustering) will be employed to classify patients into homogeneous subgroups. These patient clusters will serve as the basis for subsequent supplement design, analyses of intervention response and biomarker discovery. The dietary supplement will be formulated by selecting two or three food groups or food components that meet the highest number of predefined criteria. The selection criteria will be: (1) components positively associated with, or predictive of, a greater number of protective variables or markers of healthier status in Alzheimer’s patients; (2) components negatively associated with, or predictive of, a greater number of disease-related markers.

The rationale for designing a supplement rather than recommending dietary modifications is to minimize disruption of habitual dietary patterns, thereby maximizing adherence to the intervention and reducing caregiver burden. In addition to supplement formulation, dietary recommendations may be provided to reduce or eliminate food components associated with unfavorable biomarkers (e.g., predictors of elevated LPS levels or other parameters of disease progression). If lack of physical activity is identified as a relevant factor, tailored recommendations will also be considered according to the patients’ physical condition.

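### The arms differ in dietary advice as well as in product, so a between-arm difference belongs to the package and cannot be credited to the supplement alone, as the protocol words it

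*Protocol article*

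**What the plan says.** Section 2.5 (Allocation) defines the arms. For the new product: "The intervention group will receive the newly designed supplement, along with tailored dietary recommendations". No condition is attached. For the control arm, which takes Souvenaid, the rule is conditional: "dietary recommendations will be provided if their usual intake does not meet the established nutritional goals for this population".

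Section 2.20 (Supplement design) describes advice in softer terms and names no arm: "dietary recommendations may be provided to reduce or eliminate food components associated with unfavorable biomarkers", with predictors of raised LPS given as an example. It adds a possible further component: "If lack of physical activity is identified as a relevant factor, tailored recommendations will also be considered". The same section explains that a supplement was preferred to dietary change so as to disturb usual eating as little as possible.

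The aim concerns the product. The Introduction says: "The overarching goal is to determine whether such a tailored supplement would exhibit greater efficacy than currently available products". Section 2.2 (Interventions) sets the "designed supplement with a standard nutritional supplement commonly used in patients with AD" and gives the purpose of the three months as evaluating the supplement's "effectiveness in modulating the microbiota, LPS levels, and butyrate production". Section 2.4 (Sample size calculation) describes the two arms by product only. Section 2.21 (Statistical analysis) labels the treatment term as personalized supplement versus control.

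**The concern.** Advice is assigned together with the product. It reaches the whole intervention arm and only part of the control arm, and its content may differ between them. The protocol's own rationale is that diet shapes the microbiota and can influence LPS and butyrate, so advice is a plausible active component. LPS, which section 2.20 names as an example of what advice might target, is also a trial outcome.

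If the results are reported under the planned label, an effect of advice would be read as an effect of the supplement. Section 2.4 says the pilot's effect sizes will inform the power of a definitive trial. If that trial tests the supplement without the advice, it would be planned on an effect that does not belong to the product. Section 3 (Discussion) lists seven limitations, and unequal advice is not among them.

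**Working it through.** **1. Arms against claim.**

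| Element | Intervention arm | Control arm | Source |
|---|---|---|---|
| Product | New supplement | Souvenaid | 2.5 |
| Dietary advice, trigger | None: given to all | Only if intake misses goals | 2.5 |
| Dietary advice, content | Tailored | Not described beyond the trigger | 2.5 |
| Advice on unfavorable-biomarker predictors | May be given, arm not named | May be given, arm not named | 2.20 |
| Physical-activity advice | Possible, arm not named | Possible, arm not named | 2.20 |
| Goal, comparison, arm description, model term | Supplement | Standard supplement or control | Introduction, 2.2, 2.4, 2.21 |

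Two elements differ between the arms by rule, and the claim names one of them.

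**2. What the contrast estimates.** Let S1 and S0 be the effects of the two products, and A1 and A0 the average effects of the advice given in each arm. If the effects add, the randomized contrast is

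(S1 + A1) − (S0 + A0) = (S1 − S0) + (A1 − A0).

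The bias in a supplement-alone claim is A1 − A0. A0 need not be zero, because some controls are advised too. The article does not say how many, so A1 − A0 is unknown in size. A two-arm design in which advice goes with arm cannot separate the two terms. The section 2.21 covariates (among them physical activity and nutritional status) do not help. Baseline values carry no information on advice received later, and adjusting for diet or activity after randomization would not recover a randomized supplement effect.

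**3. The plan's own sample size.** Inputs from section 2.4: difference 0.77 − 0.26 = 0.51, pooled SD 0.6533, effect size 0.7806, two-sided alpha 0.05, power 0.80.

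n = 2 × (1.960 + 0.842)² / 0.7806² = 25.76 per group, which rounds up to 26. The article states 25, so its figure is reproduced to within one participant. Then 25 × 1.2 = 30 per arm, as stated. This point changes none of these figures.

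**4. Illustration of the bias.** Assumptions, none of them from the article: the products do not differ (S1 − S0 = 0), and the net advice difference is d = 0.2, 0.3 or 0.4 SD. Completers: 30 × (1 − 0.20) = 24 per arm. The test is an unadjusted two-sided t-test at 0.05 with 46 degrees of freedom and noncentrality d × √(24/2) = 3.464d.

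| Assumed net advice difference | Noncentrality | Rejection, 24 per arm | Rejection, 30 per arm |
|---|---|---|---|
| 0 | 0 | 0.050 | 0.050 |
| 0.2 SD | 0.693 | 0.104 | 0.119 |
| 0.3 SD | 1.039 | 0.174 | 0.208 |
| 0.4 SD | 1.386 | 0.274 | 0.332 |

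In each row the expected estimate equals the assumed advice difference, and the planned label would credit it to the supplement.

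**The case against.** The strongest reply is that comparing packages is a legitimate design, and that this is a pilot. Section 2.4 speaks of effect sizes of the intervention, the Discussion refers to a personalized nutritional strategy, and its closing summary disclaims definitive outcomes. All of this stands, and it softens the consequence. It does not reconcile the package in 2.5 with the product-only goal, comparison, arm description and model term.

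The reply is also right about several stronger readings that a reader might infer:

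- *That the intervention arm certainly gets LPS-targeted advice and controls only general advice.* Section 2.5 does not give the content of the tailored advice. Section 2.20 says advice may be given, names no arm and mentions LPS predictors only as an example. Nothing calls the control advice general; it depends on each person's intake.
- *That diet change during the intervention cannot be checked.* Section 2.3 places dietary characterization at T=0, but section 2.7 ties the 3-day record to the week of microbiota sampling, which is also planned before and after the intervention. The text is unclear on this; it does not rule out repeat measurement.
- *That sections 2.20 and 2.5 flatly contradict each other.* Section 2.20 speaks of minimizing disruption and then openly allows added advice. That is a tension in the rationale, together with a mismatch between may (2.20) and will (2.5).
- *That advice reveals the arm.* It may weaken participants' blinding to formulation, but controls can be advised too, and nothing says participants are told the advice policy by arm.
- *That the rejection rates are the trial's type I error.* They are not. The planned analyses are covariate-adjusted, with Bonferroni correction for key outcomes, and the randomized package comparison remains valid.

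**Conclusion.** The point holds as one of attribution. Under section 2.5 the trial compares supplement plus tailored advice with Souvenaid plus conditional advice, while four other sections describe a comparison of supplements. The package comparison is protected by randomization; the supplement-alone claim is not.

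The bias in that claim is the between-arm difference in advice effects. The article gives no figure for it. Rejection of about 10% to 27% at 24 per arm follows only if the net difference is 0.2 to 0.4 SD, the products are equivalent and the test is a simple t-test. It shows that a modest advice effect could matter; it does not forecast the planned analysis. A reader might conclude that the trial is invalid or that any positive result must come from the advice. The documents support neither. The physical-activity component is a possibility only, since it is conditional and no arm is named.

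**What to change.** Reconcile sections 2.5 and 2.20 with the stated aim, in one of two ways:

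1. Apply one identical advice policy to both arms from T=2 to T=3, covering diet and any physical-activity advice, with the content left to the clinical team. The product is then the only component that differs by rule.
2. Keep the present arms and restate the goal (Introduction), the comparison (2.2), the arm description (2.4), the treatment term (2.21) and all conclusions as supplement plus tailored advice versus Souvenaid plus conditional advice. Label the effect sizes passed to the definitive trial in the same way, and add the unequal advice to the limitations.

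Under either option, settle whether advice may or will be given and to which arm. Reconcile section 2.3 with section 2.7 by confirming that the 3-day food record is taken at T=2 and T=3, and report diet change by arm descriptively. This would show whether diets diverged, but it would not recover a randomized supplement-only effect.

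The cost is changes of wording and, at most, a modest extra questionnaire burden if the repeat food records are not already planned.

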### Data management

2.6

All study variables will be managed using Research Electronic Data Capture (REDCap) software (27, 28) with each participant assigned a code to ensure anonymity. The database will include all demographic and clinical variables required for the study. The first 10 data entries will be double-checked by co-investigators, a process that will also serve as additional training for data collectors. All relevant data concerning study participants and the associated measurements will be safeguarded by the principal investigator (PI), who will ensure the confidentiality and anonymity of the data at all times. All documentation related to the study will be stored in the Investigator’s File at each participating center under the custody of the PI until study completion. Once the study concludes, all documents will be indexed and transferred to the general archive of the center, following Good Clinical Practice (GCP) guidelines. The PI will ensure that subject identification codes are preserved for at least 15 years after the study’s conclusion or interruption. In all cases, the PI will guarantee the confidentiality of the data and the documents stored in the archive.

### Sociodemographic and lifestyle data

2.7

Participants’ demographic information, including age, sex, and ethnicity, as well as socioeconomic factors such as household income, number of household members, and education level will be collected. Lifestyle habits, including alcohol consumption, smoking, and contact with animals, will also be recorded. Clinical variables such as time since disease onset, age at diagnosis, and the affected brain regions will be documented, along with cerebrospinal fluid (CSF) biomarkers such as Abeta42 and phosphorylated Tau levels. Behavioral symptoms and pharmacological treatments (e.g., cholinesterase inhibitors, memantine, neuroleptics, and trazodone) will also be assessed. To evaluate dietary habits in both patients and healthy controls, a comprehensive dietary assessment will be conducted. The following validated tools will be used: a food frequency questionnaire (FFQ) (29) assessing habitual intake over the past year, a 3-day food record collected during the same week as microbiota sampling, and the 14-item Mediterranean Diet Adherence Screener (MEDAS) (30). Food intake data will be analyzed using DIAL software (version 3.15.0.0) (31) to determine intake of macronutrients, micronutrients, fiber, and other bioactive compounds, including: complex carbohydrates and simple sugars, animal and plant-based proteins, saturated, monounsaturated, and polyunsaturated fats, soluble and insoluble fiber, ethanol, and water- and fat-soluble vitamins. Physical activity will be assessed using the International Physical Activity Questionnaire for the Elderly (IPAQ-E) (32) and the Clinical Frailty Scale (CFS) (33).

### Neuropsychological assessment

2.8

To assess global cognitive function, neurologists will administer the Mini-Mental State Examination (MMSE) (34). This test evaluates several cognitive domains, including orientation, registration, attention and calculation, recall, language, and visuospatial abilities.

### Assessment of perceived stress

2.9

Participants’ perceived stress levels will be assessed using the validated 10-item Perceived Stress Scale (PSS-10) (35, 36). The PSS-10 measures the degree to which individuals perceive their lives as unpredictable, uncontrollable, and overloaded during the past month. Items are rated on a 5-point Likert scale from 0 (“never”) to 4 (“very often”), and scores are summed to provide a total perceived stress score, with higher scores indicating greater perceived stress.

### Monitoring

2.10

The Data Monitoring Committee (DMC) is composed of a multidisciplinary team including seven neurologists and five neuropsychologists. Neurologists play a central role in participant selection and in ongoing monitoring throughout the study. To identify any emerging safety concerns during the nutritional intervention, such as adverse effects, interim analyses will be conducted and may lead to protocol modifications or early termination of the trial if necessary. Interim analyses will be performed weekly during the 3-month intervention period by two members of the research team. In addition, participants will be provided with a dedicated telephone number to report any adverse events, particularly those related to gastrointestinal symptoms. This direct communication channel will ensure continued participant engagement and allow for timely detection and documentation of adverse events. The monitoring plan includes both solicited and spontaneously reported events and ensures proper documentation, evaluation, and reporting of any unintended effects arising from the study intervention.

### Biological samples

2.11

A total of 10 mL of blood will be collected in EDTA tubes by a hospital nurse and processed in hospital biobanks registered in the Spanish National Biobank Registry under reference numbers PT17/0015/0038 (HCUVA) and B0000920 (HUPHM). For stool samples, participants will be provided with materials to collect three samples (one per week for three consecutive weeks), along with an appointment for delivery. Participants will receive detailed instructions on how to collect and store the samples, including a simple, illustrated information booklet and an explanatory video. Stool collection will use Fe-Col^®^ feces collection paper (Alpha Laboratories, Hampshire, United Kingdom) and the Danastool kit (Danagen-Bioted, Badalona, Spain), which includes a tube with an integrated spoon, a participant identification label, and 8 mL of fecal DNA stabilizing reagent. This system maintains sample stability for several months at room temperature (15–25°C) and indefinitely at −20 or −80°C, allowing home collection and convenient hospital delivery. The date of sample collection and delivery will be recorded. Once in the laboratory, stool samples will be processed and stored at −80°C. One aliquot will be deposited in the hospital biobank. Stool consistency will be self-classified by participants using the Bristol Stool Scale.

### Microbiota analysis

2.12

For fecal microbiota analysis, DNA will be extracted using the Danagene Microbiome Fecal DNA kit (Danagen-Bioted, Badalona, Spain). DNA concentration will be measured using the Quant-iT™ PicoGreen^®^ dsDNA Assay Kit (Invitrogen, Waltham, MA, United States).

### Whole genome sequencing

2.13

Shotgun metagenomic sequencing will be performed on stool samples to determine microbiome composition and function. For library preparation, DNA will be randomly sheared into short fragments. The resulting fragments will undergo end-repair, A-tailing, and ligation with Illumina adapters. Adapter-ligated fragments will be size-selected, PCR-amplified, and purified. Library quality will be assessed using a Quantus™ Fluorometer (Promega, Madison, WI, United States) for quantification, and an Agilent Bioanalyzer (Santa Clara, CA, United States) for size distribution. Pooled libraries will be sequenced on the Illumina NovaSeq 6,000 platform. Raw sequencing data will be processed using the bioBakery Whole Metagenome Shotgun (wmgx) workflow, publicly available at http://huttenhower.sph.harvard.edu/biobakery (37). Quality control will be performed using the KneadData tool (v0.12.0), which includes trimming and decontamination steps. Trimming will be conducted with Trimmomatic (v0.39), using default parameters (SLIDINGWINDOW:4:20 MINLEN:50) to remove adapters, low-quality reads, and short sequences. Host-derived contaminants will be removed with Bowtie2 (v2.5.1) by aligning reads to the hg37_and_human_contamination reference database using the “very sensitive” preset, as recommended in the KneadData documentation (38, 39). Species-level microbial profiling (including bacteria, archaea, eukaryotes, and viruses) will be performed with MetaPhlAn (v4.1) using the latest database (mpa_vJun23_CHOCOPhlAnSGB_202403) (40). Functional profiling of microbial metabolic pathways and other molecular functions will be performed using HUMAnN (v3.0) (41) with the following databases: full_chocophlan.v201901_v31, uniref50_annotated_v201901b_full, uniref90_annotated_v201901b_full, uniref50_ec_filtered_201901b_subset, uniref90_ec_filtered_201901b_subset, and full_mapping_v201901b.

